### Study protocol

After inclusion, each patient will undergo three different titration procedures of the protrusive mandibular position, in a randomized order: subjective titration; RCMP titration during DISE; RCMP titration during PSG (see Fig. 1).

In our study, a commercially available RCMP (MATRx™; Zephyr Sleep Technologies Inc., Calgary, Canada) will be used [21]. The RCMP uses dental trays filled with high-viscosity impression material that fit retentively over the teeth to allow for progressive titration of the mandible during sleep, without arousing the patient. It consists of a controller that receives commands from the device software and, in turn, activates a stepping motor attached to dental trays in the patient’s mouth (Fig. 3). The positioner (50 g; 62 mm × 41 mm × 20 mm) has two movable rods that connect to brackets extending anteriorly from the dental trays. The upper rod is driven by an internal linear actuator and attaches to the upper bracket. The lower rod is driven by a manually adjustable screw and connects to the lower bracket [21]. Before the PSG-guided or DISE-assisted titration is planned, the dental sleep professional will fit upper and lower disposable dental impression trays that attach to the RCMP positioner. During that visit, the dentist will record the habitual bite position, maximum retrusion and maximum protrusion as voluntarily performed during wakefulness. These measurements will be used to set the individual’s mandibular range of motion for the RCMP studies.

**Fig. 3 Fig3:**
[figure not shown]
Schematic overview of the commercially available remotely controlled mandibular positioner (RCMP) device (MATRx™; Zephyr Sleep Technologies Inc., Calgary, Canada). Left: the controller that receives commands from the device software. Right: the motorized RCMP attached to disposable upper and lower dental impression trays. This schematic overview was drawn by our research group

#### Subjective titration

After fitting the MAD, there is a 1-month period during which patients titrate their MAD. Each patient will individually be instructed and trained to perform the actual titration of the MAD. In general, the degree of mandibular advancement is progressively increased until a significant improvement or resolution of symptoms occurs, or until the patient cannot tolerate any further advancement.

#### Titration during drug-induced sleep endoscopy (DISE) — DISE-assisted titration

The DISE will be performed by an ENT surgeon experienced in DISE in order to visualize the dose-dependent effect of the mandibular protrusion on the upper airway collapsibility. The DISE is performed in a semi-dark and silent operating theater with the patient lying in a supine position. The different collapsible levels of the upper airway that can be investigated during DISE are the palate (velopharynx), the oropharynx, the tongue base, the hypopharynx and the epiglottis. The degree of collapse at each level is reported as none, partial or complete. The pattern of the pharyngeal collapse during the obstructive events is classified as concentric, anteroposterior and/or laterolateral [35].

Upon connection of the RCMP to a dedicated laptop, calibration of the actual versus the software-guided protrusion is verified using the RCMP ruler and proprietary developed software to rule out day-to-day variation caused by environmental factors such as room temperature or humidity. This procedure ensures the mandibular displacement is read out correctly from the ruler present on the upper tray fitted over the tooth arcs (Fig. 3). After the calibration, the RCMP trays are fitted in an edge-to-edge position to avoid excessive muscle tension. A flexible fiberoptic nasendoscope (Type ENF-GP; Olympus Europe GmbH, Hamburg, Germany) will be introduced by the ENT surgeon in the awake patient to evaluate the awake upper airway state. Thereafter, sedation will be induced by intravenous administration of midazolam (bolus injection of 1.0–2.0 mg) and propofol using a target-controlled infusion system (2.0–3.0 μg/ml mean effect site concentration). The transition to unconsciousness similar to stage 2 sleep is aimed at and examined by ensuring an absence of patients’ eyelash reflex after stimulation by means of a gentle brush. Findings are noted using a uniform upper airway scoring system evaluating the level of snoring, presence of apneas, degree of oxygen saturation, degree and configuration of obstruction(s) and the level of upper airway collapse [36].

When target sedation is reached, examined by ensuring an absence of patients’ eyelash reflex after stimulation by means of a gentle brush, the RCMP will be remotely protruded in increments of 2 mm in response to the visualized upper airway collapse at the different collapsible levels until a stable upper airway together with an absence of oxygen desaturation and snoring is reached.

If a stable upper airway without oxygen desaturation and snoring is noted, the mandible will be remotely retruded for 1 mm. If the upper airway remains stable, further so-called ‘reversed titration’ will continue. This approach will be repeated until the effective target protrusive position can be determined, defined as the minimal mandibular threshold position corresponding to a stable upper airway in the absence of snoring, oxygen desaturation and apneas. When a stable upper airway is reached, the titration procedure will be fine-tuned in smaller steps (0.5 mm) to be as precise as possible.

After every protrusive or retrusive movement, the RCMP protrusion will be checked on the RCMP ruler versus the protrusion measured by the software, ensuring correct positioning of the mandible during the upper airway assessment.

If the DISE is scored as ‘predicted success’, the predicted effective target protrusive position is provided to the dentist to start MAD therapy in that position. If the DISE-assisted titration is inconclusive or scored as ‘predicted failure’, the MAD will be set at the most optimal protrusive position with the most open and stable upper airway following the medical doctor performing the DISE procedure. If the DISE procedure is inconclusive in the entire range of motion, the MAD will be set at 75% of maximal protrusion, in analogy with PSG-guided titration.

#### Titration during polysomnography (PSG) — PSG-guided titration

The mandibular protrusion titration PSG will be performed using the RCMP device, MATRx, during a standard type I, full-night, attended PSG. The PSG recordings and the scoring are performed using the AASM 2012 rules [8].

At the start of the PSG, the participant’s dental trays are attached to the mandibular positioner of the RCMP device, and the positioner is calibrated to the PSG system using the device software as explained earlier.

The titration procedure itself was previously described by Remmers et al. [21]. Once in stage 2 sleep based on the PSG signals, the patient’s mandible will be protruded remotely in 0.5-mm steps in response to evidence of apneas and/or hypopneas. If an electroencephalographic (EEG) arousal occurs, no further advancement will be attempted until stable sleep resumes. Stepwise mandibular protrusion will continue until respiratory events are reduced to normal in all sleep stages, in both supine and lateral positions, or until maximal protrusion is reached. Afterwards, an independent researcher will score the PSG together with body position and mandibular position signals, and will predict success or failure with MAD therapy, based on the predetermined interpretative rules described by Remmers et al. [21].

The patient should have REM sleep for ≥ 5 min in the supine position or in the lateral position if REM in the supine position was not observed. All REM cycles will be evaluated to identify a minimum 5-min interval where ≤ 1 respiratory event occurs. If this is the case, the PSG will be scored as ‘predicted MAD success’ for that protrusive position. If not, the PSG will be judged to predict ‘therapeutic failure’. The predicted effective target protrusive position is the minimum protrusive position that is associated with ≤ 1 respiratory event per 5-min REM sleep.

If the PSG is scored as ‘predicted success’, the predicted effective target protrusive position is provided to the dentist to start MAD therapy in that position. If the PSG is scored as ‘predicted failure’, an alternative position equal to 75% of maximal protrusion is provided. If the PSG-guided titration was scored as ‘inconclusive’ due to a lack of REM sleep, this will be incorporated into our database, but the MAD will be set at the most effective protrusive position found in non-REM sleep.

#### Sleep study

A level 1 sleep study will be planned at baseline and to assess the efficacy of the MAD treatment in the titrated positions. For the DISE-assisted and PSG-guided titration, the patients will use the MAD in the obtained protrusion during 1 month before the follow-up sleep study, while the subjective titration will be performed during a 1-month period directly followed by the follow-up sleep study (see also Fig. 1). A washout period of at least 1 week is inserted between the polysomnographic evaluation of the protrusive position obtained during a titration procedure and the start of the next titration procedure.

The follow-up sleep study will be scored by an independent sleep technician who is blinded to the treatment phase.

The results of the different polysomnographic evaluations will be discussed with the patient by the multidisciplinary team, together with an interview about the patient’s experience of snoring and daytime sleepiness and possible side effects of MAD treatment.

#### Measurement of MAD adherence

A temperature-sensitive microsensor with on-chip integrated read-out electronics (Theramon®; Handels- und Entwicklungsgesellschaft, Handelsagentur Gschladt, Hargelsberg, Austria) will be embedded in the MAD on the upper right side. Objective compliance measurement is based on the assumption that the OA is worn when a temperature ≥ 35 °C is recorded. At every follow-up visit, the objective MAD adherence will be collected.

### Outcome measures

#### Primary outcome

The protrusive position that was predicted as the effective target protrusive position during each titration method (subjective titration, PSG-guided titration PSG and DISE-assisted titration) will be assessed and compared between the different titration methods.

#### Secondary outcomes

Efficacy of the MAD therapy will be assessed as a measure of treatment outcome by comparing the baseline AHI with the AHI under MAD therapy.

In addition, structured questionnaires to evaluate tolerance and side effects, subjective snoring, daytime sleepiness and fatigue will be completed by all patients at baseline and at follow-up evaluations.

The degree of daytime sleepiness will be assessed using the Epworth Sleepiness Scale (ESS) [37]. A standard 10-point visual analog scale (VAS) for the scoring of snoring as assessed by the bed partner will be used only in patients who have a bed partner who is able to report the snoring intensity. This VAS is ranging from 0 to 10, with 0 equaling no snoring and 10 causing the bed partner to leave the room or sleep separately [38]. Heavy snoring will be defined as a VAS snoring index of at least 7. Fatigue severity will be measured by the Checklist Individual Strength (CIS20R) [36]. The CIS20R, and more specifically its subscale on fatigue, is a standardized and validated questionnaire that consists of eight items scored on a 7-point Likert scale. The scores range from 8 (normal fatigue) to 56 (most severe fatigue). A score of 26 or lower indicates a normal energy level, scores between 27 and 35 indicate mild fatigue and a score of 36 or higher indicates severe fatigue.

For all secondary outcomes, non-inferiority of RCMP titration with PSG compared to RCMP titration with DISE will be assessed. Additionally, differences between subjective titration and both RCMP titration protocols will be investigated.

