**Discussion:**

Currently, the optimal titration of MAD therapy is most often based on ‘trial and error’. The conventional method relies on subjective improvement in symptoms, although this may not provide the most accurate indicator for efficient titration. Therefore, relying on objective criteria in the titration process should be advantageous. In analogy with CPAP, titration of the most optimal mandibular protrusion could be performed using RCMP during an overnight titration PSG. Recently, it was shown that titration under direct visualization of upper airway patency and collapsibility is feasible using the RCMP during DISE. However, no clinical results for such a procedure are as yet available. This study is the first to compare the most optimal mandibular protrusive position according to three titration procedures, as well as to compare the therapeutic efficacy of these titration methods.

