#### Statistical analyses

The primary endpoint and all continuous secondary endpoints will be analyzed using a linear mixed-effects model with period, sequence and procedure as fixed effects, and a patient nested within sequence as a random effect. For the response rate, a logistic mixed-effects model with the same specifications will be used. The response rate will be defined as a decrease in AHI of at least 50% compared to baseline or an AHI under treatment of < 15 events/h. Post-hoc comparisons will be made based on these models, correcting for multiple testing by means of Bonferroni–Holm stepdown correction.

Non-inferiority of PSG compared to DISE will be judged based on the confidence intervals obtained from the mixed-effects models. When the lower limit of the confidence interval falls above the predefined non-inferiority margin, non-inferiority will be concluded. The non-inferiority margin for the percent change in AHI from baseline will be set at 10%. For the change in VAS for snoring, the ESS, the CIS20R and its fatigue subscale the margin is considered, respectively, to be 1, 2, 5 and 10 points. Additionally, differences between subjective titration and both RCMP titration protocols will be investigated for all of the secondary endpoints.

If more than 20% of all information regarding one endpoint is missing, a sensitivity analysis will be conducted for this endpoint using multiple imputation. Results of the original analysis will be interpreted in the light of these sensitivity analyses.

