## Discussion

Mandibular advancement devices are a valuable nonsurgical treatment option for patients diagnosed with OSA. The literature has shown that the amount of mandibular protrusion is a key factor in optimizing MAD efficacy and that the final titration of the protrusion should be carried out individually, trying to find the most effective protrusion, whilst at the same time respecting the patient’s physical limits [20, 39]. However, there is still no consensus on the optimal titration method.

The conventional approach relies on improvement of subjective symptoms, such as snoring and/or daytime sleepiness, for guidance of the titration toward the ideal mandibular protrusion in the individual OSA patient [24–27].

A more objective approach includes the use of an RCMP during a full-night PSG: in a process analogous to a CPAP titration night, the mandible is progressively advanced during sleep each time respiratory events occur throughout the night [21]. However, this is a time-consuming, labor-intensive and expensive procedure, because of the need for an overnight and attended hospital stay [12].

Civelek et al. [12] studied the effect of modulated CPAP pressure on upper airway collapsibility under direct visualization applying DISE. This DISE-assisted titration showed comparable results regarding the optimal CPAP pressure that alleviates OSA as compared to the conventional titration PSG. However, the titration procedure during DISE was found to be less labor-intensive and time-consuming as compared to a titration PSG [12].

The present randomized crossover trial will assess the mandibular protrusion values of MAD treatment under DISE-assisted titration using RCMP and compare these to the values obtained using a titration PSG, as well as with those obtained using the conventional subjective titration method. Furthermore, if different mandibular protrusion values are obtained according to the studied titration methods, it will be possible to compare the efficacy using level 1 sleep studies recorded at the end of each procedure.

Ideally, the same titration protocol for the DISE-assisted titration and the titration PSG is considered. However, due to the technical limitations of both procedures, some minor adaptations were made to the DISE-assisted titration protocol compared to the titration PSG as described earlier in the Methods section of this manuscript.

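### The secondary non-inferiority hypothesis is worded as PSG against DISE, opposite to the article's rationale, and the unsigned lower-limit rule does not settle which direction is tested

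*Protocol article*

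**What the plan says.** The direction is given twice in the protocol article. Secondary outcomes states that "non-inferiority of RCMP titration with PSG compared to RCMP titration with DISE will be assessed" for all secondary outcomes. Statistical analyses states: "Non-inferiority of PSG compared to DISE will be judged based on the confidence intervals obtained from the mixed-effects models". In both places PSG-guided titration is the method under test and DISE-assisted titration is the reference.

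The decision rule follows: "When the lower limit of the confidence interval falls above the predefined non-inferiority margin, non-inferiority will be concluded". The AHI margin is 10 percent. The margins for the other scales are 1 for the snoring VAS, 2 for the ESS, 5 for the CIS20R and 10 for its fatigue subscale. The margins carry no sign. The article does not say which method is subtracted from which, whether outcomes enter as raw changes or as reductions, or what the confidence level is.

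On the standing of the two methods, the Abstract says of RCMP titration during DISE: "However, no clinical results for such a procedure are as yet available". The Background credits RCMP titration, which it introduces as a technique of overnight sleep studies, with a larger AHI reduction than conventional titration. The Discussion calls titration PSG slow, laborious and costly, and reports from a CPAP study that "the titration procedure during DISE was found to be less labor-intensive and time-consuming as compared to a titration PSG". The closing paragraph of the Discussion mentions non-inferiority of the procedures without a direction. Nowhere does the article state a test of DISE as non-inferior to PSG.

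**The concern.** A non-inferiority test guards against one error only: declaring the tested method acceptable when it is worse than the reference by more than the margin. On the article's own account, the open question is whether the newer DISE procedure does acceptably well next to PSG-guided titration. As worded, the test guards against PSG being worse than DISE and gives no protection against DISE being worse.

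Efficacy in terms of AHI, snoring, sleepiness and fatigue is assessed only through the secondary outcomes, so these tests carry whatever the trial will formally claim about the relative efficacy of the two RCMP methods. A positive result in the stated direction could be read as support for DISE when it is not. The missing sign convention adds a second problem, because under one natural coding the written rule tests a different hypothesis from the one stated beside it.

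**Working it through.** **1. The plan's own figure.** The only stated size is 65 patients for 80% power on the primary equivalence endpoint (margin 1.6, SD 3.7, significance level 0.05/3 = 0.0167). For paired two one-sided tests with a true difference of 0:

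n = [3.7 × (z(0.9833) + z(0.90)) / 1.6]² = [3.7 × (2.128 + 1.282) / 1.6]² ≈ 62.2, so 63.

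The exact t-based search gives 65, with power 80.5%. The stated 65 is reproduced. Equivalence is symmetric in the two methods, so this figure does not depend on the direction discussed here. The article gives no power for the non-inferiority tests.

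**2. Inputs for the non-inferiority test.** From the article: n = 65 and a margin of 10 for percent change in AHI, taken as percentage points. Assumed, because the article gives no figure: a two-sided 95% confidence interval, and an SD of the within-patient difference in percent AHI change of 20, 30, 40 or 50 points. A paired comparison stands in for the mixed model.

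**3. Coding A: percent reduction, higher is better.** Let d be the number of points by which DISE is truly worse than PSG, and SE = SD/√65 (2.48, 3.72, 4.96 and 6.20 for the four SDs).

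- Stated test: contrast PSG minus DISE, true value +d. It succeeds if the lower limit exceeds −10. The probability is P(T > t(0.975; 64)), with T non-central t on 64 df and non-centrality (d + 10)/SE.
- Reverse test: contrast DISE minus PSG, true value −d, same limit. The non-centrality is (10 − d)/SE.

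Probability of success, stated test / reverse test:

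| SD | d = 0 | d = 5 | d = 10 | d = 20 |
|---|---|---|---|---|
| 20 | 0.978 / 0.978 | 1.000 / 0.510 | 1.000 / 0.025 | 1.000 / <0.001 |
| 30 | 0.754 / 0.754 | 0.978 / 0.262 | 1.000 / 0.025 | 1.000 / <0.001 |
| 40 | 0.510 / 0.510 | 0.846 / 0.167 | 0.978 / 0.025 | 1.000 / <0.001 |
| 50 | 0.355 / 0.355 | 0.664 / 0.122 | 0.888 / 0.025 | 0.997 / <0.001 |

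In every row the stated test gains, or stays at 1.000, as DISE worsens, while the reverse test loses. With equal methods the two have the same chance of success.

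**4. Coding B: raw change from baseline, lower is better.** Percent change in AHI, the snoring VAS, the ESS and the CIS20R all improve downwards. Take PSG minus DISE in raw change with a margin of −10. If DISE is d points worse, the true contrast is −d. The lower limit then exceeds −10 with non-centrality (10 − d)/SE, which is the reverse test of step 3: 0.025 at d = 10 and below 0.001 at d = 20. Under this coding the written rule tests DISE against PSG, contrary to the hypothesis it is meant to implement.

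**5. Side by side.** Under coding A, rule and hypothesis agree, but the hypothesis runs against the rationale. Under coding B, the rule suits the rationale but contradicts the hypothesis. The text fixes neither coding.

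**The case against.** The strongest reply is that the consequence depends on a coding the article does not give. That stands. A reader might infer that the planned test will certainly succeed even if DISE is clearly worse. The article does not support this as a fact, because its lower-limit rule applied to raw changes would do the opposite. What is certain is that the stated hypothesis conflicts with the rationale and that the rule does not settle the direction.

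A reader might also infer that a positive result would say nothing about DISE. That goes too far. The judgement rests on confidence intervals, and the other limit of the same interval shows how much worse DISE could be. Post-hoc comparisons are also planned. A 20-point deficit would be 20/6.20 = 3.2 to 20/2.48 = 8.1 standard errors over the assumed SDs, so it would be visible. The formal conclusion is misdirected, but the information is not lost.

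Nor does the article name PSG as the control. The Background says no titration standard has been proven, and the labour and time advantage of DISE comes from CPAP titration, not MAD titration. This weakens any description of PSG as an established reference. It does not remove the asymmetry: one method has earlier outcome evidence, and for the other only feasibility has been reported. The article offers no argument for making PSG the method that must prove itself.

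An unseen analysis plan does not answer the point either. The article states a direction twice, so a plan with the other direction would contradict it.

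**Conclusion.** Wrong as written; should-fix. Both statements of the hypothesis point away from the question the article motivates, and the decision rule either confirms that direction or contradicts it, depending on an unstated coding.

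Under the coding that matches the stated hypothesis, the test succeeds with probability 0.888 to 1.000 when DISE is worse by exactly the margin, against 0.025 for the reverse test. When DISE is 20 points worse the figures are 0.997 to 1.000 against less than 0.001. These rest on 65 evaluable patients, a two-sided 95% interval and assumed SDs of 20 to 50 points. The pattern holds across that range.

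A reader might infer that the trial's main conclusion is compromised. It is not: the primary endpoint is equivalence of protrusive position, which has no direction, and the sample size was set for that endpoint. The effect is confined to the secondary non-inferiority claims.

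**What to change.** - In Secondary outcomes and in Statistical analyses, state the hypothesis as non-inferiority of DISE-assisted titration compared with PSG-guided titration.
- Define the contrast as DISE minus PSG in change from baseline, and note that lower is better for AHI, VAS, ESS and CIS20R.
- Conclude non-inferiority when the upper limit of the confidence interval, at a stated level, lies below the positive margin: +10 percentage points for AHI and the margins already given for the other scales. Equivalently, code the outcomes as reductions and require the lower limit of DISE minus PSG to lie above the negative margin.

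The hypothesis and the rule must change together. Keeping the present lower-limit rule with DISE minus PSG on lower-is-better scales would again make the test easier to pass the worse DISE is.

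The cost is a few sentences. Data collection and sample size do not change, and if the methods are equally effective the chance of success is the same in either direction (step 3, d = 0). The change should be made and dated before any results by procedure are seen, because reversing a hypothesis afterwards would not be credible.
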